### Other measurements

Additional measurements of changes from baseline are evaluated, including height and weight at weeks 26 and 52, and changes in severity of concomitant disorders and health problems at weeks 26 and 52.

### Rationale for sample size

The sample size was determined on the basis of the primary outcome measure, GMFM-66. Using a 2-sided test, a sample size of approximately 37 children per treatment would assure 80 % power to detect a difference of at least 1.6 points (α = 0.05) assuming a standard deviation of 2.2 and dropout rate of 0.2. This mean change of 1.6 points in GMFM-66 scores was considered a clinically meaningful change in previous studies [17, 19]. We also planned the sub-group analyses considering disease severity measured by GMFCS (2 sub-groups, I-III and IV-V) and age (2 sub-groups, <3 and ≥3) heterogeneity. Therefore, a total of 300 participants will be required.

### Statistical and analytical plans

The study will present both descriptive and comparative results of conventional treatment and TKM combination treatment. In this study, we define operationally the conventional treatment (CT) group as children who have received only PT, OT, ST, and other conventional therapies, whereas the TKM combination treatment (CT + TKM) group is defined as children who have received at least twelve sessions of any type of acupuncture or 30 days of herbal medication within a 6-month follow-up period in addition to conventional therapies. At the time of analysis, participants will be classified in the conventional or TKM combination treatment group based on the six-month or one-year follow-up information (Fig. 2).

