## Methods/Design

### Study design

The study team is conducting a one-year, multi-site, prospective observational study of rehabilitation for children with CP. We are recruiting the children at two university-affiliated hospitals, one TKM hospital and three TKM clinics. The children with CP receive treatments from doctors and therapists in each clinic or centre, and one independent investigator assesses functional changes in participants and collects survey documents from their guardians or parents. We will analyse changes in the children’s functional development and health condition, the number of adverse events, and monetary resources spent for rehabilitation during this period. This design is a comparative observational study of a conventional treatment group and a TKM combination treatment group (Fig. 1).

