### Participant eligibility

The study subjects are children with CP aged 6 to 78 months. Because the Paediatric Evaluation of Disability Inventory (PEDI) assessment module is suitable for children under the age of seven, we defined the upper age criterion considering the one-year follow-up period. Children who have had orthopaedic surgery due to CP; children who have congenital muscular disease, hereditary disease, or progressive central nervous system diseases; and children who suffer from severe diseases (i.e., cancer, severe heart disease, or severe infectious disease) are excluded from this study.

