### Treatment

The participants undergo rehabilitation according to their doctors’ clinical care, but they do not receive any intentional treatments. During the period, they can freely start, cease or change any conventional treatments or TKM treatments. The conventional treatments can include PT, OT, ST and other conventional therapy, and the TKM treatments include herbal medicine, chuna, moxibustion and any type of acupuncture, e.g., body acupuncture, scalp acupuncture and pharmacopuncture. The most frequent set of TKM treatments implemented for CP children in South Korea is acupuncture and/or herbal medicine.

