#### Participant survey

Parents or guardians respond to survey questionnaires. Data are collected using surveys conducted at baseline, mid-study, and end of study, and monthly tracking surveys will also be used. A baseline interview survey consists of basic characteristics, cause of CP, concomitant disorders, health problems, surgical history, medication, rehabilitation therapies, TKM treatment, health supplements, and medical care cost. An interview survey conducted on the 26th and 52nd weeks will include questions on concomitant disorders and health problems. The monthly tracking survey obtains information on health problems, changes in rehabilitation and treatments, medical care cost, and quality of life (QOL) with the Peds-QL CP module (ver 3.0) [10]. These guardian-reporting documents are collected and managed by the Clinical Research Center of Pusan Korean Medicine Hospital each month for a year. After the parents or guardians complete the forms, the investigators ensure that there are no blank spaces. In the case of insufficient data, we will check the accuracy of the information by reviewing medical records.

We will translate the PedsQL CP module (ver 3.0) into a Korean version and perform concurrent validation and reliability studies.

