**Fig. 2 Fig2:**
[figure not shown]
Process and time line of the observational study. CT, conventional treatment; TKM, traditional Korean medicine; ATx, acupuncture; Mx, medication

For the analysis of effectiveness, multiple variables, including age, severity of illness (indicated by the GMFCS), and treatments, will be converted to propensity scores by logistic regression, and the two groups will be compared by matching or stratification. We expect that using propensity scores will enhance the control variables of heterogeneous conditions. The last observation carried forward method will be used to handle missing data. The change from baseline of the GMFM-66 and PEDI scores at weeks 26 and 52 will be representative outcomes to evaluate effectiveness. These outcomes will be analysed by a two-sample *t*-test for the cross-sectional dataset and by a linear mixed model for the longitudinal dataset [20].

For sub-group analysis, we will analyse the correlation between rehabilitation intensity and functional changes in each group. We will also examine the different outcomes between acupuncture and acupuncture plus herbal medication cases in the TKM combination treatment group.

The number of participants with SAEs and non-SAEs will be reported via analysis of frequency, and the detailed progress of SAEs and related health problems will be disclosed as safety issues. In the case of long-term medication, we will carefully investigate adverse drug reactions using the drug-induced liver injury causality assessment scale [21].

The effectiveness of TKM reported by guardians will be used for further patient-centred outcome research. In the case of participants ceasing TKM treatments, we will investigate the reasons to enhance the feasibility of developing an RCT protocol.

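### The CT + TKM group counts only TKM received during follow-up, so children already on TKM at registration are pooled with new starters, a structural risk of bias of unknown size and direction

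*Protocol article*

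**What the plan says.** Under Statistical and analytical plans, the combination group is "children who have received at least twelve sessions of any type of acupuncture or 30 days of herbal medication within a 6-month follow-up period", on top of conventional therapies. The comparator is "children who have received only PT, OT, ST, and other conventional therapies". Assignment is made at analysis: "participants will be classified in the conventional or TKM combination treatment group based on the six-month or one-year follow-up information". Neither definition mentions TKM use before or at registration.

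Participant eligibility lists surgical and disease exclusions only, beginning "Children who have had orthopaedic surgery due to CP; children who have congenital muscular disease, hereditary disease, or progressive central nervous system diseases" and ending with severe disease. Prior TKM is not restricted and no washout is set. On sites, Study design says "We are recruiting the children at two university-affiliated hospitals, one TKM hospital and three TKM clinics". Under Treatment, "they can freely start, cease or change any conventional treatments or TKM treatments".

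TKM use is recorded at registration. The baseline interview in Participant survey covers "surgical history, medication, rehabilitation therapies, TKM treatment, health supplements, and medical care cost", and Table 1 marks TKM treatment at baseline and every month.

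The primary outcomes are changes in GMFM-66 and PEDI from study baseline to weeks 26 and 52. Safety is the number of participants with serious and non-serious adverse events in the study period. For confounding, "multiple variables, including age, severity of illness (indicated by the GMFCS), and treatments, will be converted to propensity scores by logistic regression". The planned sub-group analyses concern GMFCS level, age, rehabilitation intensity, and acupuncture with or without herbal medicine. None separates new from continuing TKM use.

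**The concern.** The rule gives the same label to two kinds of child. For a new starter, baseline comes before TKM, and change from baseline covers the whole response. For a continuing user, baseline is a point partway through treatment: gain already made is in the baseline score, and early adverse events lie before the counting window. Children who tried TKM and gave it up before registration are not in the combination group at all. Because the CT definition gives no look-back period, they may be counted as CT.

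The distortions can pull in opposite directions. Gain already in the baseline pulls the difference towards zero. Selective retention of children who respond to or tolerate TKM could push it in favour of CT + TKM. Early harms that fall outside the window would make CT + TKM look safer.

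The Discussion intends the results to inform a guideline and a future randomised trial. A trial would ordinarily test starting TKM, which a mixture of starting and continuing does not estimate cleanly.

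**Working it through.** **1. The plan's own figure.** Inputs from Rationale for sample size: difference 1.6, SD 2.2, two-sided α 0.05, power 80%, dropout 0.2.

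- n per group = 2 × (1.960 + 0.842)² × 2.2² / 1.6² = 29.7, so 30.
- After dropout: 29.7 / 0.8 = 37.1, which matches the stated 37.
- Two groups × four sub-group cells × 37 = 296, about the stated 300.

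The sample size is not in error. It implies 300 × 0.8 / 2 = 120 evaluable children per group overall and about 30 per group in each cell, if groups and cells are equal. Equal split is an assumption, since groups form by actual treatment and matching may discard children.

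**2. Effect of pooling.** Two quantities are not in the documents and are assumed: p, the share of CT + TKM children already on TKM at baseline, and r, the fraction of the 1.6-point gain they still make afterwards. This models dilution only, not selective retention, and leaves the SD at 2.2.

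Expected difference = 1.6 × [(1 − p) + p × r]. Standard error = 2.2 × √(2/120) = 0.284 overall and 2.2 × √(2/30) = 0.568 in a cell. Power is by normal approximation.

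| p | r | Difference | Power, 120 per group | Power, 30 per group |
|---|---|---|---|---|
| 0 | – | 1.6 | >99% | 80% |
| 25% | 0 | 1.2 | 99% | 56% |
| 25% | 0.5 | 1.4 | >99% | 69% |
| 50% | 0 | 0.8 | 80% | 29% |
| 50% | 0.5 | 1.2 | 99% | 56% |
| 75% | 0 | 0.4 | 29% | 11% |
| 75% | 0.5 | 1.0 | 94% | 42% |

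The t-test version is about a point lower in the cells: 28% and 55% for the two 50% rows.

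**3. What a new-starter contrast would retain.** True difference 1.6, standard error 2.2 × √(1/n₁ + 1/n₂):

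- 60 starters versus 120 CT: SE 0.348, power 99.6%.
- 30 starters versus 120 CT: SE 0.449, power 95%.
- One cell, 15 versus 30: SE 0.696, power 63%.
- One cell, 7.5 versus 30 (the average cell size with 30 starters overall): SE 0.898, power 43%.

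The two overall figures keep all 120 CT children. Removing those with TKM at baseline lowers them somewhat: with 90 CT children left (an assumption), they become 99% and 93%.

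**The case against.** The strongest case on the other side has five parts.

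*This is a usual-care study.* One-year change with versus without TKM, continuing users included, is a legitimate question. That stands, and it is why the full comparison should stay. But continuing users' change does not answer the question of starting TKM, and no planned result would show how far the two differ.

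*The propensity score may already include baseline TKM.* Its variable list is open and names treatments without saying which or when. So it cannot be said that the baseline item goes unused. Adjustment would still not recover the period before baseline. If baseline TKM nearly determines group membership, it would also leave little overlap for matching.

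*A sensitivity analysis is detail for the SAP.* A condensed article may leave such detail out. The group definition, however, is stated here, and it is this definition that pools the two kinds of user.

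*The bias is asserted, not shown.* A reader might infer that the effectiveness and safety comparisons are biased, that most CT + TKM children are continuing users, or that adverse events are under-counted because those who did badly had already left. The documents support none of these as fact. They give no share of baseline users, no time course of effect, and no account of children who stopped before entry. The distortions may partly cancel. Safety is to be reported by frequency, with no between-group test stated.

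*Absence of TKM at baseline is an imperfect criterion.* It leaves in children who stopped shortly before registration, and true starters may begin at any time in follow-up. Both limits stand. The article does not say whether the baseline survey records past use. Fig. 2, cited for the classification, is not available here, although the text definition is explicit.

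**Conclusion.** The point holds as a structural risk. Applied as written, the rule pools continuing users with new starters. Baseline under treatment and a study-period count of adverse events mean that the two contribute different information. Four TKM providers among six sites, and a TKM item in the baseline survey, make continuing users likely, but their share is unknown.

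Size and net direction cannot be derived from the documents. Over the ranges assumed, dilution alone takes the expected difference from 1.6 to between 0.4 and 1.4. At a 50% share, overall power is 80% or 99%, depending on whether continuing users gain nothing more or keep half the gain. Serious loss overall therefore needs a high share together with little residual gain. The sub-group cells are more exposed. These figures rest on equal groups, an unchanged SD of 2.2 and no selective retention, which could move the estimate the other way.

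This is worth acting on because the remedy is cheap. It is no ground for rejecting the planned comparison.

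**What to change.** Keep the full comparison and the stated group definition. In addition:

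1. Use the TKM item from the baseline survey to split CT + TKM into new starters (no TKM at baseline) and continuing users.
2. Pre-specify new starters versus CT children without TKM at baseline as a sensitivity analysis of the overall comparison, for GMFM-66, PEDI and adverse events. Report it beside the full result.
3. Show baseline TKM status in the balance table.
4. If the baseline survey records past use, apply a stated look-back period in both groups, so that children who stopped just before registration do not count as unexposed. If it does not, state this as a limitation.

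The core split needs no new data collection. The price is fewer children and a wider interval: the standard error rises from 0.284 to 0.348 with 60 starters or 0.449 with 30, against 120 CT children. Overall power for 1.6 points stays at about 99% and 95%, somewhat less once CT children with baseline TKM are removed. With about 63% power at 15 versus 30, the contrast should not be carried into the sub-group cells.

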**Fig. 2 Fig2:**
[figure not shown]
Process and time line of the observational study. CT, conventional treatment; TKM, traditional Korean medicine; ATx, acupuncture; Mx, medication

For the analysis of effectiveness, multiple variables, including age, severity of illness (indicated by the GMFCS), and treatments, will be converted to propensity scores by logistic regression, and the two groups will be compared by matching or stratification. We expect that using propensity scores will enhance the control variables of heterogeneous conditions. The last observation carried forward method will be used to handle missing data. The change from baseline of the GMFM-66 and PEDI scores at weeks 26 and 52 will be representative outcomes to evaluate effectiveness. These outcomes will be analysed by a two-sample *t*-test for the cross-sectional dataset and by a linear mixed model for the longitudinal dataset [20].

For sub-group analysis, we will analyse the correlation between rehabilitation intensity and functional changes in each group. We will also examine the different outcomes between acupuncture and acupuncture plus herbal medication cases in the TKM combination treatment group.

The number of participants with SAEs and non-SAEs will be reported via analysis of frequency, and the detailed progress of SAEs and related health problems will be disclosed as safety issues. In the case of long-term medication, we will carefully investigate adverse drug reactions using the drug-induced liver injury causality assessment scale [21].

The effectiveness of TKM reported by guardians will be used for further patient-centred outcome research. In the case of participants ceasing TKM treatments, we will investigate the reasons to enhance the feasibility of developing an RCT protocol.

Medical costs will be analysed for distribution characteristics, and we will perform a descriptive analysis of quantitative data. Each variable will be verified by statistical sensitivity and value analysis. Constant tariff values of the initial QOL measurements will be used to estimate QALYs between each follow-up interval, and a straight line of final QOL measurements will be used for extrapolation. An incremental cost-effectiveness ratio table and a cost-effectiveness plane will provide mean values of parameters, and a probabilistic sensitivity analysis will be conducted using distributions of estimated values of major variables. The analyses will be based on a societal perspective, and the discount rate will be 5 % based on the reference case recommendation of the Panel on Cost-Effectiveness in Health and Medicine and the Guidelines of Economic Evaluation of Medical Supplies in South Korea.

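### The propensity score admits treatments with no time limit, although treatment received in follow-up defines the groups, and the t-test on change scores has no stated link to the strata or pairs and no adjustment for the baseline score

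*Protocol article*

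**What the plan says.** All references are to the protocol article.

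- **Group definition** (Statistical and analytical plans). The combination group consists of children who reach a minimum amount of acupuncture or herbal medication within a six-month follow-up period, on top of conventional therapy. The comparison group has conventional therapies only. Children are classified at the time of analysis, from six-month or one-year follow-up information.
- **Freedom to change** (Treatment). During the study, "they can freely start, cease or change any conventional treatments or TKM treatments".
- **Propensity score** (Statistical and analytical plans, after Fig. 2). There, "multiple variables, including age, severity of illness (indicated by the GMFCS), and treatments, will be converted to propensity scores by logistic regression". Neither the kind nor the timing of the treatments is given, and the list is open-ended. On how the score is then used, the text says only that "the two groups will be compared by matching or stratification".
- **Outcome analysis** (same paragraph). The outcomes are changes from baseline in GMFM-66 and PEDI at weeks 26 and 52. For cross-sectional data the plan names an ordinary t-test between the groups ("These outcomes will be analysed by a two-sample"). Longitudinal data go to a linear mixed model.
- **What is available** (Table 1 and Participant survey). Conventional treatment, TKM treatment, concomitant disorders, GMFCS, GMFM-66 and PEDI are all recorded at baseline. The two treatment items are also recorded every month.

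**The concern.** A propensity score balances groups on what was known before exposure. A variable that defines the exposure, or that may respond to it, does not belong in the score. The first destroys the overlap needed for matching or stratification. The second can adjust away part of the effect or introduce new bias, because therapy during follow-up may depend on TKM use or on how the child is progressing. The text as written admits both kinds.

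The second part is how the score reaches the result. A score used to form strata removes confounding only if the strata enter the comparison. The test named for the change scores is an ordinary two-sample t-test, and nothing says how strata or pairs enter it or the mixed model. Taking a change score subtracts the baseline value. It does not adjust for children at different starting levels having different expected gains.

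This matters because the study is not randomised. It covers children aged 6 to 78 months with a wide range of severity, and the sample size section itself recognises heterogeneity by age and GMFCS.

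**Working it through.** **1. The plan's own figure.** Inputs from Rationale for sample size: "Using a 2-sided test", α = 0.05, 80% power, difference 1.6, "assuming a standard deviation of 2.2 and dropout rate of 0.2".

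n per group = 2 × [2.2 × (1.960 + 0.842) / 1.6]² = 29.7. Allowing for dropout, 29.7 / 0.8 = 37.1, which reproduces the stated 37. Then 37 × 2 groups × 4 sub-group cells = 296, close to the stated 300. This is the sample size of an unadjusted two-sample comparison, consistent with the planned t-test.

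**2. Three readings of treatments in the score.**

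| Reading | Consequence |
|---|---|
| TKM received in follow-up | Predicts group by definition |
| Conventional therapy in follow-up | Post-exposure variable |
| Therapy recorded at baseline | Legitimate covariate |

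The first reading was checked by simulation: 300 children, half in each group, with follow-up acupuncture sessions set to 0 in one group and at least 12 in the other, and age and GMFCS also in the logistic model. Fitted scores were below 0.001 in every conventional-treatment child and above 0.999 in every combination child. That leaves nothing to match or stratify on.

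**3. A t-test over all children after stratification.** The inputs other than the SD, the total of 300 and the dropout rate are assumptions. Evaluable children: 300 × 0.8 = 240, taken as 120 per group. There is no true effect, the SD within stratum is 2.2, two strata differ by 2 points in mean change, and 40% of one group and 60% of the other are in the faster stratum.

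- Bias = 2 × (0.60 − 0.40) = 0.40 points.
- Variance per child = 2.2² + 2² × 0.4 × 0.6 = 4.84 + 0.96 = 5.80.
- Standard error = √(2 × 5.80 / 120) = 0.311.
- Bias / standard error = 1.29.
- Type I error = Φ(1.29 − 1.96) + Φ(−1.29 − 1.96) ≈ 25%.

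Simulation gave 26% without the stratum and 5% with the stratum in the model. Over gaps of 1 to 3 points and mixes of 45/55 to 35/65, the unstratified error ran from 6% to 76%.

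**4. An unpaired t-test after matching.** With within-pair correlation ρ (assumed), the true size is 2 × [1 − Φ(1.96 / √(1 − ρ))]. This gives 0.039 at ρ = 0.1 and 0.006 at ρ = 0.5, against a nominal 0.05. The test is conservative.

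**5. Precision from baseline adjustment, in one sub-group cell.** At 30 evaluable children per group, the standardised difference is (1.6 / 2.2) / √(1 − R²), where R² is the share of variance in change explained by baseline covariates (assumed). Power from the t distribution:

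| R² | Power |
|---|---|
| 0 | 79% |
| 0.2 | 87% |
| 0.3 | 91% |
| 0.5 | 97% |

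For the main comparison, the unadjusted test already has power above 99.9% at 120 v 120 and about 99.8% at 60 v 180.

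**The case against.** The strongest reply is that the worst readings are unlikely. Group is the dependent variable of the logistic model, so few analysts would enter follow-up TKM as a predictor of itself. Both groups receive conventional therapy, and the baseline interview records it, so the authors may have meant baseline conventional therapy, which is a sound covariate. This stands as far as it goes: a reader might infer that the score is certain to be invalid, and the documents do not show that. But the text does not state the valid reading. The Discussion speaks of counting interventions and sessions to calculate intensity for statistical analysis, and it does not settle the timing.

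A reader might also infer that the t-test ignores the strata or pairs, so that the score does nothing. That goes beyond the text. The same paragraph says the groups are compared by matching or stratification, and a t-test could be run within strata or on a matched sample. What can be said is that no link is stated. A full protocol or SAP may give it. Nor is the t-test the only analysis, since a mixed model is also planned.

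Three further inferences fail:

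- An unpaired test after matching does not produce false benefit. It is conservative.
- Baseline is not wholly disregarded. The outcome is a change score, GMFCS is in the propensity score, and the covariate list is open.
- The main comparison is not short of power. The precision argument applies only to the sub-group cells.

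**Conclusion.** The point holds in this limited form. The protocol names a propensity covariate that is clearly valid under only one of three readings and does not say which one is meant. In a study where follow-up treatment defines the groups, the sole stated confounding control should not be left open in that way. An unseen SAP might narrow the term, but the published text affirmatively includes it without restriction.

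The t-test part is conditional. If it is run over all children after stratification, confounding stays in the estimate. The bias of 0.40 points and type I error of about 25% show what that could mean, on assumed stratum differences and mixes. If it is run unpaired after matching, the cost is lost power, not bias. The documents give no data from which the actual confounding could be sized, so no estimate of it is offered against the 1.6-point target. The gain in power from 79% to 87–97% rests on assumed R² of 0.2 to 0.5 and applies only to a sub-group cell of 30 per group.

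**What to change.** In Statistical and analytical plans:

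1. State that the propensity score is estimated only from variables known at registration: age, GMFCS, baseline GMFM-66 and PEDI, concomitant disorders, and conventional therapy and TKM use as reported in the baseline survey. State that treatments received in follow-up are excluded from the score.
2. Replace the unadjusted two-sample t-test with a regression of the change score on group, propensity stratum (or matched pair), baseline score, age and GMFCS.
3. Specify the linear mixed model with the same terms.

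The cost is analysis wording only. Every variable named is already scheduled at baseline, so no visit, questionnaire or participant is added. The change should be made before outcomes are compared between the groups.

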#### Investigator assessment

A qualified investigator visits the sites to measure each participant’s height and weight and classify each child according to the Gross Motor Function Classification System (GMFCS). The investigator is not a treatment provider nor an employee of any hospital or clinic, and this constitutes unbiased evaluation.

Gross motor function is assessed using the Gross Motor Function Measure-66 (GMFM-66) and the PEDI. All measurements and assessments will be performed at baseline and at the 26^th^ and 52^nd^ weeks. In this study, we will use the Korean versions of the GMFCS [11], GMFM-66 [12], and PEDI [13], which have undergone validity and reliability studies [14].

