### Primary outcome measurement

The first primary outcome is the changes from baseline of the GMFM-66 scores at weeks 26 and 52. The GMFM-66 includes 66 items identified through Rasch analysis, which collectively best describe gross motor function in children with CP of varying abilities [15, 16]. The second primary outcome is the changes from baseline of the PEDI scores at weeks 26 and 52. The PEDI uses 217 questions to measure abilities in the three functional domains of self-care, mobility and social function [17].

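### Last observation carried forward is the only stated method for missing GMFM-66 and PEDI scores; it shrinks a real difference and biases the comparison if loss to follow-up differs by group

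*Protocol article*

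**What the plan says.** The missing-data rule is one sentence in the Protocol article, Statistical and analytical plans: "The last observation carried forward method will be used to handle missing data". It is not limited to one outcome or one analysis. The same paragraph then plans to analyse change in GMFM-66 and PEDI by a two-sample t-test for the cross-sectional dataset and "by a linear mixed model for the longitudinal dataset".

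Primary outcome measurement makes both scores primary at both visits: "The first primary outcome is the changes from baseline of the GMFM-66 scores at weeks 26 and 52" and "The second primary outcome is the changes from baseline of the PEDI scores at weeks 26 and 52". Under Investigator assessment, "All measurements and assessments will be performed at baseline and at the 26^th^ and 52^nd^ weeks". Participant eligibility covers a wide developmental range: "The study subjects are children with CP aged 6 to 78 months". Rationale for sample size assumes a "dropout rate of 0.2", without splitting it by group.

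The check for blanks and the review of medical records, under Participant survey, concern the guardians' forms and not the GMFM-66 or PEDI assessments.

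**The concern.** Carrying the last value forward assumes that a child's score stays flat after the last visit. That is hard to defend in children of this age, in a study whose stated purpose includes following their development (Study design: "We will analyse changes in the children’s functional development and health condition"). With three assessments, only two values can be carried. A baseline carried forward gives zero change at weeks 26 and 52. A week-26 score carried forward gives the half-year change at week 52.

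The error in each group is proportional to the follow-up lost and to the growth missed. If loss is equal, a real effect is diluted. If loss is unequal, a difference appears where none exists, in the direction that favours the better-followed group. Groups are formed from treatment received during follow-up, so early loss need not fall evenly on them.

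**Working it through.** **Inputs from Rationale for sample size.** Difference 1.6, SD 2.2, two-sided alpha 0.05, power 80%, dropout 0.2, 37 per treatment, 300 in total.

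**Assumptions, because the documents give no figure.** Mean one-year gain G of 2 to 5 points; growth and treatment effect roughly linear over the year; f = share of dropouts who have only a baseline score.

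**1. The plan's own figure.** n = 2 × (1.96 + 0.84)² × 2.2² / 1.6² ≈ 29.7 per group; 29.7 / 0.8 = 37.1, which agrees with 37. Then 37 × 2 groups × 4 subgroups = 296, close to 300. The sample size reproduces.

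**2. Share of the yearly change lost.** With dropout d, L = d × [f + (1 − f)/2]. At d = 0.2:
- no dropout has week 26 (f = 1): L = 0.20
- half have it (f = 0.5): L = 0.15
- all have it (f = 0): L = 0.10

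**3. Equal dropout.** The expected difference is 1.6 × (1 − L):

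| Dropouts with week 26 | Expected difference | Power at 37 per group |
|---|---|---|
| none | 1.28 | 71% |
| half | 1.36 | 76% |
| all | 1.44 | 80% |

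Power is by normal approximation with the SD held at 2.2 and all 37 children analysed. With no true effect, both groups lose G × L and the difference stays 0.

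**4. Unequal dropout, no true effect.** False difference (combination minus conventional) = −G × (L_combination − L_conventional). Ten percentage points more loss before week 26 in one group gives 0.1 × G, that is 0.2 to 0.5 points for G = 2 to 5, or 12.5% to 31% of 1.6. If the extra loss comes after week 26, it is 0.05 × G.

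**5. The group rule.** The combination group needs twelve acupuncture sessions or 30 days of herbal medication. Take 20% dropout spread evenly over 12 months in everyone, no effect, and children who start traditional treatment but leave below the threshold excluded.
- Conventional: 10% lost before week 26 and 10% after, so L = 0.10 + 0.05 = 0.15.
- Combination, threshold met at 3 months: 5% excluded; L = (0.05 + 0.05)/0.95 = 0.105. Bias = 0.045 × G, or 0.09 to 0.22 points for G = 2 to 5.
- Combination, threshold met at 1 month: 1.67% excluded; L = (0.0833 + 0.05)/0.9833 = 0.1356. Bias = 0.014 × G, or 0.03 to 0.07 points.

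Both favour combination treatment.

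**6. Observed-data model for comparison.** Simulation with 150 per group, 400 runs, G = 3, half of dropouts with baseline only, and dropout random within group:

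| Dropout (conventional/combination) | True difference | Carried forward | Likelihood model, observed data |
|---|---|---|---|
| 20%/20% | 0 | 0.00 | 0.00 |
| 10%/30% | 0 | −0.46 | −0.01 |
| 30%/10% | 0 | 0.44 | −0.01 |
| 20%/20% | 1.6 | 1.35 | 1.59 |
| 10%/30% | 1.6 | 0.80 | 1.60 |
| 30%/10% | 1.6 | 1.93 | 1.60 |

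The unequal splits are illustrations and are not forecasts for this study.

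**The case against.** Several counter-arguments have force.

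- **The sizes rest on assumptions.** The documents give neither the natural gain nor dropout by group. This stands, and it is why only ranges are given. A gain as large as 8 points would be 3.6 times the planned SD of 2.2 and is not used here.
- **Equal dropout is conservative.** It creates no false effect. At about 150 per group, even 1.28 gives 1.28 / (2.2 × √(2/150)) = 5.0 standard errors, so power exceeds 99%. This stands: the loss of power matters for comparisons of subgroup size. The overall estimate is still too small.
- **The group rule.** A reader might infer that a child lost in the first months can never be in the combination group, and hence a large built-in bias. The text does not support that: 30 days of herbal medication also qualifies and can be completed in about a month. Nor can all early losses be placed in the conventional group, which is limited to children who had conventional therapies only; a child who began traditional treatment and left below the threshold fits neither definition. Classification uses six-month or one-year information, so it is also unclear whether children lost before six months are classified at all. If they are not, most zero-change entries leave the comparison.
- **The mixed model.** A reader might infer that carrying forward defeats it. That follows only if the filled values enter the longitudinal dataset. The article separates the two datasets and does not say. If they do enter, the model loses its validity under missing at random and precision is misstated.

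None of this rescues the method. It is named without limit, so this is not a detail left to an analysis plan, and the zero entered for a baseline-only child is exact.

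**Conclusion.** The point holds in limited form. Followed as written, the plan enters zero or about half of the yearly change for children lost to follow-up, on both primary outcomes. With equal 20% dropout, a true 1.6 becomes 1.28 to 1.44 and a true null stays unbiased. With 10 percentage points more early loss in one group, the false difference is 0.1 × the mean yearly gain, or 0.2 to 0.5 points for an assumed 2 to 5. The group rule can add about 0.014 to 0.045 × the gain in favour of combination treatment, if sub-threshold children are excluded and dropout is spread evenly over the year.

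The half-gain figure needs roughly linear growth; the zero does not. The documents support no particular false-positive rate, and harm to the mixed model is conditional on how the sentence is read.

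**What to change.** Remove carrying forward as the main method for missing GMFM-66 and PEDI scores. State that the planned linear mixed model, fitted to all observed scores at baseline, week 26 and week 52 without imputation, is the main analysis, with group, visit, group-by-visit, age and GMFCS. Keep the planned propensity-score matching or stratification. Report missingness by group and visit. Add multiple imputation and a sensitivity analysis for scores missing not at random. Carrying forward may remain as a secondary sensitivity analysis at most. How children lost before six months are classified should be stated alongside, because this change does not settle it.

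The cost is a few sentences and a little more analysis work, with no new data and no change in sample size. The main result would rely on missing at random, which the sensitivity analysis is there to test.
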